### Statistical analysis

Data will be analysed using mixed-effects models, incorporating fixed effects (intervention group) and random effects (participant-level variability). Stratification variables (age and gender) will be included as covariates to adjust for stratified randomisation. Additional analyses will include χ^2^ tests for categorical variables, analysis of variance (ANOVA) for continuous variables and linear regression models to explore associations between clinical outcomes and potential predictors. All analyses will be performed on an intention-to-treat basis.

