### Sample size calculation

The sample size calculation is based on findings from our prior randomised controlled trial evaluating Sphinx pose yoga therapy in healthcare professionals with CLBP.^17^ In that study, participants in the yoga group showed a significant improvement in functional disability, with a mean reduction of 4.4 points on the Oswestry Disability Index (ODI) and an SD of 3.69, corresponding to an effect size (Cohen’s d) of approximately 1.2. For the current study, we have conservatively assumed a smaller effect size of 0.6 to ensure adequate power even if the true effect is more modest. This value is consistent with effect sizes commonly reported in the literature on mind-body interventions such as yoga and MBSR for CLBP. Using a significance level of 0.05 and a power of 0.80, the required sample size is 44 participants per group. To account for a potential 20% dropout rate, the final sample size has been increased to 55 participants per group, totalling 220 participants across the four study groups (figure 1).

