### Outcome measures

Outcome measures will be assessed at baseline (week 0), at the end of the intervention (week 12) and 12 weeks after the intervention (week 24).

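### The stated mixed model has no visit-specific treatment effect and no baseline adjustment; if week 0 is fitted as a response, its group coefficient is diluted by one third

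*Protocol article*

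**What the plan says.** The Statistical analysis section of the protocol article sets out the main model: "Data will be analysed using mixed-effects models, incorporating fixed effects (intervention group) and random effects (participant-level variability". The covariates follow: "Stratification variables (age and gender) will be included as covariates to adjust for stratified randomisation". It names no visit term, no group-by-visit term and no baseline value of the outcome.

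The Outcome measures section sets the visits: "Outcome measures will be assessed at baseline (week 0), at the end of the intervention (week 12) and 12 weeks after the intervention (week 24". One of the three precedes treatment and two follow it.

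The Sample size calculation section plans on a single standardised difference: "we have conservatively assumed a smaller effect size of 0.6 to ensure adequate power even if the true effect is more modest". It continues: "Using a significance level of 0.05 and a power of 0.80, the required sample size is 44 participants per group". It does not tie that difference to a visit.

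The article does not say whether the week-0 value enters the model as a response, whether the response is a change score, or which visit carries the primary comparison.

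**The concern.** In a randomised trial with one pre-treatment and two post-treatment measurements, the treatment effect lies in the differences between arms after baseline. A model whose only design term is group has a single coefficient for each pair of arms, and that coefficient is a weighted average over whichever visits are fitted. It cannot separate an effect at the end of treatment from one that persists 12 weeks later, which is what the second follow-up is there to show.

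A participant random effect needs repeated rows, the three visits are listed together as outcome assessments, and baseline is absent from the covariates. Fitting all three visits is therefore a natural literal reading. On that reading the average includes a visit at which the expected difference is zero, so both the estimate and the power fall below what the sample size was planned for. The same model would serve all the primary outcomes.

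**Working it through.** **Inputs.** From Sample size calculation: d = 0.6, alpha 0.05 (sidedness not stated; taken as two-sided), power 0.80, 44 evaluable per group, 20% dropout. From Outcome measures: visits at weeks 0, 12 and 24. Assumed, because the article gives none: within-person correlation ρ of 0.3, 0.5 or 0.7, equal between all pairs of visits, and SD 1 at each visit.

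**The plan's own figure.** n = 2(1.960 + 0.842)²/0.6² = 43.6, so 44 per group. Allowing for dropout, 44/0.80 = 55, and 4 × 55 = 220. Power at 44 is 80.4%. The sample size reproduces.

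**Reading 1: all three visits are responses.** With complete data and a participant random intercept, the group coefficient is the difference in participant means over the three visits:

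- expected value = (0 + d12 + d24)/3
- SE = √[2(1 + 2ρ)/(3n)], which at n = 44 is 0.156, 0.174 and 0.191 for ρ = 0.3, 0.5 and 0.7

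| Effect at week 12, week 24 | Coefficient | Below week-12 effect | Power at ρ = 0.3 / 0.5 / 0.7 |
|---|---|---|---|
| 0.6, 0.6 | 0.40 | 33% | 73% / 63% / 56% |
| 0.6, 0.3 | 0.30 | 50% | 49% / 41% / 35% |
| 0.6, 0 | 0.20 | 67% | 25% / 21% / 18% |
| 0.6, 0.9 | 0.50 | 17% | 90% / 82% / 75% |

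In every row the coefficient is exactly one third below the mean of the two post-treatment effects. To restore 80% power in the sustained case, 53, 66 or 79 evaluable participants per group would be needed.

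*Dropout after baseline.* Suppose 55 per group start and 11 contribute week 0 only. Each visit of the 44 completers has weight 44/(1 + 2ρ), and the extra baseline rows add 11. At ρ = 0.5 the sustained-case coefficient is (22 × 0.6 × 2)/(3 × 22 + 11) = 26.4/77 = 0.34. Over ρ = 0.3 to 0.7 it runs from 0.35 to 0.33, which is 41% to 44% below 0.6.

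*Simulation check* (ρ = 0.5, sustained effect, 44 per group, 150 runs). The mean group-only coefficient was 0.417. The Monte Carlo standard error is about 0.174/√150 = 0.014, so this agrees with 0.40. Adding a visit main effect left it at 0.417. Giving each follow-up visit its own group contrast, with a common baseline mean, gave 0.603 at week 12.

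**Reading 2: only weeks 12 and 24 are responses.** The expected value is (d12 + d24)/2, and SE = √[2(1 + ρ)/(2n)], which is 0.185 at ρ = 0.5. The coefficient is 0.60 if the effect is sustained, 0.45 if it halves and 0.30 if it vanishes. Power at ρ = 0.5 is about 90%, 68% and 37%.

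**Baseline-adjusted week-12 contrast.** SE = √[2(1 − ρ²)/n], which is 0.203, 0.185 and 0.152. For d = 0.6 the power is about 84%, 90% and 98% at ρ = 0.3, 0.5 and 0.7, whatever happens by week 24.

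**The case against.** The article is a condensed account and no analysis plan is shown. Its sentence does not say that group is the only fixed effect, and the parenthesis may be shorthand for the treatment factor in a fuller model. Visit terms and covariance structure are often left to the analysis plan. This has force, but the article does more than defer: it lists the fixed effect, the random effect and the covariates by name, and the term that would carry a visit-specific effect is not among them. ANOVA is also mentioned, but as an additional analysis with no visit or baseline handling attached.

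Three stronger inferences are tempting and are not supported.

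- A reader might infer that the plan commits itself to averaging in baseline. Nowhere does it say that week 0 is a response row. With follow-up values or change scores as responses, a sustained effect is recovered at 0.60.
- A reader might infer that the effect is always understated by a third or more. Against week 12 this fails if the effect grows: with 0.9 at week 24 the shortfall is 17%. The exact one third is relative to the mean post-treatment effect, with complete data.
- A reader might count the whole distance from the 84% to 98% of a baseline-adjusted contrast as loss. The plan promised 80%; the part above that is a gain from using baseline. At ρ = 0.3 the sustained-case shortfall from plan is 7 points.

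Which visit is primary is also for the sponsor to decide; the article designates none.

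**Conclusion.** The concern holds, in conditional form. What does not depend on any assumption is that the model as written gives no treatment effect specific to week 12 or week 24 and makes no adjustment for the baseline value.

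The size depends on the handling of week 0. As a response row, it pulls the group coefficient one third below the mean post-treatment effect with complete data, and further with dropout after baseline; sustained-case power falls to about 56% to 73% over the assumed correlations. If week 0 is left out, the remaining fault is the blending of two visits, which matters to the extent that the effect changes between them. These figures rest on SD 1 at each visit, equal correlation between visits, and d = 0.6 at week 12. The sample size figure itself is not in error.

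**What to change.** State the main model as follows. The responses are the week-12 and week-24 values. The fixed effects are group, visit, group-by-visit, the baseline value of the outcome, age and gender, and within-participant correlation is allowed for. Keeping week 0 as a response with a baseline mean common to all arms serves the same purpose. Report the between-group contrast at each follow-up visit, and have the sponsor name the primary one in advance; week 12, when treatment ends, is a natural choice. Adding a visit main effect alone is not enough, because it leaves the dilution in place.

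The cost is one paragraph of wording in the protocol or analysis plan. It needs no new data, visits or participants.

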### Randomisation

Randomisation will be conducted using computer-generated sequences, stratified by key demographics (eg, age, gender).

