### Interventions

Participants will be randomly assigned to one of four intervention groups (see table 1).

**Table 1 T1:** Detailed intervention protocols and session schedules across study groups

Group	Intervention	Description	Duration/frequencies/sessions
Group A	Sphinx pose yoga therapy	Participants will engage in Sphinx pose yoga therapy, focusing on back extension poses. The programme follows a simplified protocol aimed at improving accessibility, adherence and safety, especially for high-risk occupational groups.^17^ Sessions include warm-up stretching, targeted back extension and cool-down, with a focus on minimalism to ensure clinical benefit.	Frequency: 3 times per week for 12 weeks
			Session duration: 40 min per session
			Total sessions: 36 sessionsTotal contact time: 24 hours
Group B	MBSR (mindfulness-based stress reduction)	Participants will engage in a structured MBSR programme, including mindfulness meditation, body scan exercises, gentle yoga-based movements and group discussions. The programme follows the standard 8-week MBSR curriculum, extended to 12 weeks to match the duration of other interventions.^31^ Participants will be encouraged to practise daily at home using guided recordings.	Frequency: 1 session per week for 12 weeks
			Session duration: 2 hours per session (weeks 1–8), 1 hour per session (weeks 9–12)
			Total sessions: 12 sessionsTotal contact time: 20 hours
Group C	Usual care	Participants will receive guidance based on The Back Book, which includes advice on remaining active, avoiding prolonged rest and using simple pain control methods like over-the-counter analgesics. The approach encourages low-impact exercises (eg, walking, swimming) and basic stress reduction strategies, such as relaxation and breathing techniques.	Frequency: As per individual need, based on standard care guidelines
			Duration: 12 weeks
			Total sessions: Minimal contact, no structured sessions

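### MBSR has a group component in Groups B and D, but the stated model and sample size make no allowance for correlation within classes; site is also not named in the model, which costs precision only

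*Protocol article*

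**What the plan says.** All references are to the protocol article.

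- **Delivery.** Table 1 (Interventions) describes Group B's programme as "including mindfulness meditation, body scan exercises, gentle yoga-based movements and group discussions", in 12 weekly sessions. The Group D row gives that arm the same MBSR schedule on top of the full yoga programme. Group C has no structured sessions. Class size, number of instructors, and whether B and D sit in the same classes are not stated. Nor is it stated whether yoga is taught in groups.
- **Model.** Statistical analysis describes mixed-effects models with intervention group as the fixed effect and "random effects (participant-level variability") on the random side, plus age and gender as covariates. No class, instructor or site term is named.
- **Sample size.** "Using a significance level of 0.05 and a power of 0.80, the required sample size is 44 participants per group", from this premise: "we have conservatively assumed a smaller effect size of 0.6". Then: "To account for a potential 20% dropout rate, the final sample size has been increased to 55 participants per group". No ICC or design effect appears.
- **Site.** Study design calls the trial multicentre. The Randomisation section reads: "Randomisation will be conducted using computer-generated sequences, stratified by key demographics (eg, age, gender"). Site is not in that list, which is given by way of example. Statistical analysis then identifies the stratification variables as age and gender.

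**The concern.** People who spend 12 weeks in the same MBSR class share its members, its discussions and probably its instructor, so their outcomes may be more alike than those of people in different classes. A participant random effect deals with repeated measures on one person at weeks 0, 12 and 24. It does nothing for correlation between people in the same class.

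If that correlation is positive, the variance of an MBSR arm mean is larger than the model believes. Usual care has no such clustering, so the error runs one way: intervals for B or D against C are too narrow and p-values too small, and MBSR is declared different from usual care too often. The planned power is overstated for the same reason.

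Site is a separate and milder matter. In a multicentre trial, differences between sites that are neither balanced by design nor modelled stay in the residual.

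**Working it through.** **1. Reproduce the plan's figure.** Inputs from Sample size calculation: effect size d = 0.6, alpha 0.05 (taken as two-sided, since sidedness is not stated; a one-sided test would give 35), power 0.80.

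n = 2 × (1.960 + 0.842)² / 0.6² = 43.6, so 44 per group. Dropout: 44 / 0.80 = 55. Total: 4 × 55 = 220. All three figures reproduce under full independence. Exact-sum power at 44 is Φ(0.6 / √(2/44) − 1.96) = 80.4%.

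**2. Allow for class clustering.** Class size m and ICC are assumptions. If 55 are randomised into 5 classes, m = 11 at randomisation and 44 / 5 = 8.8 among completers. Alternatively, 44 completers in 4 classes give m = 11. ICC is taken as 0.01 to 0.05.

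- Design effect: DE = 1 + (m − 1) × ICC.
- Variance factor: V = (1 + DE) / 2 when one arm is clustered (B or D versus C).
- Actual type I error: 2 × [1 − Φ(1.96 / √V)].
- Power with the correct standard error, 44 per arm: Φ(0.6 / √(2V/44) − 1.96).

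| m | ICC | DE | V | true SE / model SE | type I error | power |
|---|---|---|---|---|---|---|
| 8.8 | 0.01 | 1.08 | 1.04 | 1.02 | 5.5% | 79% |
| 8.8 | 0.02 | 1.16 | 1.08 | 1.04 | 5.9% | 77% |
| 8.8 | 0.05 | 1.39 | 1.20 | 1.09 | 7.3% | 73% |
| 11 | 0.01 | 1.10 | 1.05 | 1.02 | 5.6% | 78% |
| 11 | 0.02 | 1.20 | 1.10 | 1.05 | 6.2% | 77% |
| 11 | 0.05 | 1.50 | 1.25 | 1.12 | 8.0% | 71% |

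In the last row, restoring 80% power needs 43.6 × 1.25 = 54.5, so 55 evaluable per arm, or 55 / 0.80 = 69 randomised. With a wider range (m = 8 to 15, ICC 0.01 to 0.10), type I error runs from 5.4% to 13.3% and power from 79% to 58%. At ICC 0 there is no effect.

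**3. B versus D.** If the arms attend separate classes, V = DE. At ICC 0.02 to 0.05, type I error is 6.8% to 9.6% with m = 8.8 and 7.4% to 11.0% with m = 11. Power at m = 11 is 73% to 63%. If B and D share classes, the class effect is common to both arms. Simulating 8 shared classes of 11 with 44 per arm, the unadjusted test rejected about 5.0% of the time at ICC 0.02 and about 4.5% at 0.05, so there was no inflation.

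**4. Site omitted from the model.** Simulated with individual randomisation, 4 sites, 44 per arm, site ICC 0.05 to 0.20, and 20,000 runs per setting. Type I error was 5.0% to 5.1% when arms were not balanced by site. When they were balanced, it fell from 4.5% to 3.7%. At ICC 0.20 with balanced arms, the model standard error was 0.207 against a true 0.193, so it was slightly too large.

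**The case against.** **This is a condensed article, and a class or site term could sit in the full protocol or analysis plan.** That is possible. The sentence on the model is plainly shorthand: it lists no time term although outcomes are measured at three points, and it does not say that participant is the sole random effect. But it does name model terms, and the sample size does state its assumptions. Followed as written, the analysis ignores class. If a fuller document already has the term, the correction is one sentence.

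**The size rests on assumed inputs.** This stands. Class size, instructors and ICC appear nowhere in the protocol, and the range begins at negligible. The figures show sensitivity and do not estimate what will happen.

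**A reader might infer that every contrast involving B or D is anti-conservative.** The document does not support that. Nothing says that classes are arm-specific, and with shared classes B versus D is not inflated. The B versus D figures hold only for separate classes.

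**A reader might also infer that omitting site makes standard errors too small, or confounds the comparison.** Neither follows. Individuals are randomised, so chance site imbalance is random error that the standard error already covers, and the simulation shows valid or slightly conservative tests. Site could add to the problem only through classes confined to one site, which is the class effect again, or through treatment effects that differ by site. Nor can one say flatly that site is not a stratum, since the Randomisation list is illustrative. The inference rests on Statistical analysis naming only age and gender.

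**Conclusion.** The point holds in limited form. Two of the four arms receive a treatment with a group component, and neither the stated model nor the sample size allows for it. For B or D against usual care, any positive within-class correlation makes standard errors too small. With about 9 to 11 per class and an ICC of 0.01 to 0.05, the standard error is understated by about 2% to 12%, type I error is about 5.5% to 8%, and power is about 79% to 71%. These results depend on assumed class sizes and correlations, and on the normal approximation with 44 evaluable per arm.

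B versus D is affected similarly or more only with separate classes. Yoga versus MBSR has B on one side, so the arithmetic for one clustered arm applies if yoga is taught individually; if yoga is taught in groups, Group A is clustered too.

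Omission of site is a matter of precision and chance balance, not of validity. This should be changed because the remedy is cheap and class membership may be hard to recover if it is not recorded during delivery. It does not show that the trial's conclusions would be wrong.

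**What to change.** 1. Record MBSR class and instructor for every participant in B and D, and yoga class if yoga is taught in groups.
2. State whether B and D attend the same MBSR classes.
3. In Statistical analysis, add a random effect for class in the group-delivered arms only (a partially nested model), with small-sample degrees of freedom.
4. Add site as a fixed effect and, if randomisation has not begun, as a stratum. Whether age remains a stratum is a matter of preference and not part of this point.
5. In Sample size calculation, say that 80% power assumes no clustering, and give the power for a stated range of class sizes and ICCs.

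The cost is an identifier field, some wording, and possibly a regenerated randomisation list. The statistical price is wider intervals for MBSR contrasts, and with few classes it is not trivial. With 5 classes per arm and DE of 1.2 to 1.5, a Satterthwaite approximation gives about 13 to 11 degrees of freedom for B versus C. The interval multiplier is then √1.10 × 2.17 / 1.96 = 1.16 to √1.25 × 2.21 / 1.96 = 1.26, so intervals are about 16% to 26% wider than the unadjusted ones. Power under this analysis is therefore somewhat below the figures above, which use the normal quantile. More, smaller classes would reduce the loss where delivery allows.

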### Biochemical assessment

Blood samples for biomarkers (cortisol, β-endorphins, substance-P, IL-6, CRP) will be collected at three points: baseline (week 0), post-intervention (week 12) and follow-up (week 24), between 08:00 and 09:00 in a fasting state to minimise diurnal and metabolic variability. Participants will be instructed to avoid vigorous physical activity, caffeine and analgesics 12–24 hours before sampling. The collected samples will be centrifuged within 30 min and stored at −80°C. All biomarkers will be analysed using standardised ELISA kits following international protocols.

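### The mixed model makes no stated provision for the outcome's own baseline value, which costs precision or, if week 0 is a response under a group-only effect, dilutes the treatment effect

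*Protocol article*

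**What the plan says.** The Statistical analysis section makes a mixed-effects model the main analysis. It names one fixed effect, intervention group, and a participant-level random effect. On covariates it says: "Stratification variables (age and gender) will be included as covariates to adjust for stratified randomisation". It then lists additional analyses, among them "analysis of variance (ANOVA) for continuous variables". It mentions no baseline value of the outcome, no time term and no group-by-time term, and it does not say whether week 0 is part of the response.

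The baseline values will exist. The Outcome measures section schedules all outcomes at weeks 0, 12 and 24, and the Biochemical assessment section says that the blood samples "will be collected at three points: baseline (week 0), post-intervention (week 12) and follow-up (week 24".

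The Sample size calculation section plans on a standardised difference ("we have conservatively assumed a smaller effect size of 0.6") and concludes: "Using a significance level of 0.05 and a power of 0.80, the required sample size is 44 participants per group".

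**The concern.** The baseline value of an outcome is usually among the best predictors of its later value. Age and gender are unlikely to stand in for it, particularly age, since eligibility is restricted to 25–45 years. A model that names its covariates but leaves this one out risks giving up power that the planned visits have already paid for.

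A second risk arises because the model has a participant random effect and three measurement times. An analyst could reasonably enter week 0 as one of the repeated responses. With group as the only treatment term, the group coefficient then averages over a visit at which, by randomisation, no treatment difference is expected. That changes what is estimated as well as how precisely.

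**Working it through.** **Inputs.** From the Sample size calculation section: effect size 0.6, significance level 0.05, power 0.80, dropout 20%, four equal arms. The significance level is taken as two-sided, which the article does not state; a one-sided test would need 35 per group and does not match. The correlation ρ between baseline and follow-up is not given, so a range is assumed. Except in step 3, 0.6 is read as a difference in SDs of the follow-up score. All power figures use the normal approximation.

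**1. The plan's own figure.** n = 2(1.960 + 0.842)² / 0.6² = 43.6, so 44 per group. 44 / 0.80 = 55, and 4 × 55 = 220. All three reproduce, using an unadjusted two-group comparison. Power at 44 per group is Φ(0.6 / √(2/44) − 1.960) = 80.4%.

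**2. Follow-up values only, one visit.** Baseline adjustment multiplies the variance of the contrast by 1 − ρ²:
- ρ = 0.4: 0.84, a cut of 16%
- ρ = 0.5: 0.75, a cut of 25%, equivalent to 1/0.75 = 1.33 times the participants
- ρ = 0.7: 0.51, a cut of 49%

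**3. If 0.6 is on a change-score scale.** The prior trial is summarised as "a mean reduction of 4.4 points on the Oswestry Disability Index (ODI) and an SD of 3.69", and 4.4 / 3.69 = 1.19. If that SD is the SD of change and 0.6 is on the same scale, baseline is already partly used. Adjustment then multiplies the variance by (1 − ρ²) / [2(1 − ρ)] = (1 + ρ)/2, which is 0.70 at ρ = 0.4 and 0.85 at ρ = 0.7. The cut is 30% to 15%.

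**4. Week 0 as a response.** Assume complete data, equal correlation between visits, 44 per group, and true differences of 0, 0.6 and 0.6 at weeks 0, 12 and 24.
- *Group effect only:* the estimate is (0 + 0.6 + 0.6)/3 = 0.40, with variance (2/44)(1 + 2ρ)/3.
- *Group-by-time, baseline means free:* the week-12 contrast is a change-score contrast, with variance (2/44) × 2(1 − ρ).
- *Group-by-time, common baseline mean:* in this setting it equals baseline-covariate adjustment at week 12, with variance (2/44)(1 − ρ²).

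Power under each reading:

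| ρ | One follow-up visit, no baseline | Week 0 as response, group only | Week 0 as response, group-by-time, free baseline | Baseline covariate, or common baseline mean |
|---|---|---|---|---|
| 0.3 | 80.4% | 72.9% | 66.2% | 83.9% |
| 0.4 | 80.4% | 67.8% | 72.9% | 86.7% |
| 0.5 | 80.4% | 63.2% | 80.4% | 90.1% |
| 0.7 | 80.4% | 55.5% | 95.3% | 97.6% |
| 0.8 | 80.4% | 52.2% | 99.4% | 99.7% |

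The last column is the highest in every row, and it needs terms that the section does not name.

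**The case against.** The strongest reply is that this is a condensed article whose analysis plan is not shown. The sentence on age and gender explains why those two factors are in the model; it does not say that they are the only covariates. A repeated-measures model may already use week 0, and with a common baseline mean nothing is lost against covariate adjustment. Part of this stands: the article does not exclude baseline adjustment, and the plan may supply it. But the article does state a concrete model, and the reply works only with time, group-by-time and common-mean terms that it does not mention. With the one fixed effect that is named, carrying week 0 as a response makes matters worse.

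A reader might also infer three stronger things that the text does not support.
- *That continuous outcomes will be tested by an unadjusted ANOVA.* ANOVA appears only among the additional analyses. It is not described as unadjusted, as confined to follow-up, or as an efficacy test, so a contest between two efficacy answers cannot be read out of the text.
- *That the trial forgoes a rise in power from 80% to 90%.* That figure compares baseline adjustment with a single-visit, follow-up-only comparison at an assumed ρ of 0.5. The article commits to neither.
- *That chance baseline imbalance makes the analysis invalid.* Under randomisation an unadjusted follow-up comparison keeps its type I error, and its standard error already allows for chance imbalance. The loss there is of precision only.

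Transformation of skewed biomarkers is a detail for the analysis plan and is not part of this point.

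**Conclusion.** The point holds as a gap in the stated model that is worth closing before analysis. Fitted to follow-up data as written, the model gives up 16–49% of the variance of a single-visit contrast for ρ of 0.4–0.7, or 15–30% if the planned effect is on a change-score scale. With week 0 as a response and a group-only effect, a true 0.6 is estimated as 0.40, and power is 52–73% over ρ of 0.3–0.8. These sizes rest on the assumed correlations, and the diluted case also on complete data, equal correlation between visits and the same true effect at weeks 12 and 24. The sample size takes no credit for baseline, so it is neither wrong nor undermined. The text does not show that baseline adjustment has been ruled out, only that it is not provided for.

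**What to change.** In the Statistical analysis section, state that each efficacy model adjusts for the outcome's own baseline value in one of two ways:
- as a covariate in a model of the week-12 and week-24 values; or
- with week 0 as a response, a common baseline mean across arms, and group-by-time terms.

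State that the week-12 group contrast is taken from that model. Keep age and gender as covariates. State that the additional ANOVA is descriptive and is not a second efficacy test.

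This costs a few sentences in the protocol or analysis plan. It needs no new data, visits or participants.
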